**Sampling unit:** Individual patients who are HIV positive but ARV-naïve, assessed and found to be eligible to commence ART based on CD4 < 500 cells/ml and/or WHO stage 3 & 4 disease.

**Sampling method:** A simple random sampling method will be used to select eligible patients for the study.

**Random allocation:** Participants will be allocated to either of the intervention or control groups based on simple, complete randomization technique using their unique ID numbers from a random number table. An independent project biostatistician will generate 1:1 randomization numbers for study arm assignments using a random number generating program. Random allocation will consider and eliminate all forms of possible bias based on the socio-demographic characteristics of the clients.

**Allocation concealment:** Written allocation of assignment will be sealed in individual opaque envelopes marked with study identification numbers which will be available in the study clinic to allocate the target number of participants. After consenting to participate and meeting the inclusion criteria, screened subjects will be enrolled and immediately afterwards are assigned to a randomized study arm by the study coordinator opening the sealed envelopes to determine allocation. Age and gender will be assessed for balance of study arm allocation.

**Blinding:** Investigators will be blinded to intervention assignments.

**Sample size:** The formula for hypothesis testing was used (Lameshow et al., 1990).

$$n = 2d^2[Z_{1-\alpha/2} + Z_{1-\beta}]^2 \mu_1 - \mu_2$$

Where: d = estimated standard deviation (assumed to be equal for each group) is 132 cells/ $\mu$ l (Ref: 10, Table 1)

$\mu_1$  = estimated mean CD4 count increase after commencement of ART with >90% adherence is at least 50cells/ $\mu$ l (14.3%) i.e 550 $\pm$ 50

$\mu_2$  = estimated mean baseline CD4 count at commencement of ART (Based on WHO 2013 guideline of when to commence ART, which is CD4 = 500 cells/ml of blood)

$Z_{1-\alpha/2}$  = standard error when  $\alpha = 0.05$  (95% Confidence Interval) = 1.96

$Z_{1-\beta}$  = standard error associated with power = 0.842 ( $\beta = 0.20$ ) Power ( $1-\beta$ ) = 80%

Expected CD4 increase within 6 months of treatment with >95% adherence is 50 cells/ml

$n = 2 \times (132)^2 [1.96 + 0.842]^2 / (550 - 500)$

$n = 110$  which is the minimum required sample size  $110 + 10\%$  of  $110 = 121$  (attrition)

$121 \times 2 = 242$  (for experimental and control groups)

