Hence, sample size of 121 per group will be used for the study

**Intervention Protocol:** For the intervention group – a ‘reminder module’ will be developed and delivered via SMS and telephone calls by 2 PLHIV (research assistants). This will include weekly SMS medication reminders, SMS reminders 3 days prior to scheduled clinic appointments and telephone call reminders a day prior to scheduled clinic appointment (in addition to standard care – adherence counseling). To ensure confidentiality, typical medication reminder text messages will include a short slogan in Malay language “Apa khabar” “Ini untuk menberithau anda ubat” meaning “How are you?” “This is to remind you of your medications”. Appointment reminder text message would be “Apa khabar” “Tolong ingat tarikh temu janji lusa” meaning “How are you?” “Remember your appointment day after tomorrow” and telephone conversation would be standardized and short, with the message “Apa khabar” “Tolong ingat tarikh temu janji besok” meaning “How are you?” “Remember your appointment tomorrow”. The control group will receive standard care - routine adherence counseling only. Patients will not be required to provide any responses to the text messages. A call and SMS log will be recorded and kept. Two PLHIV that are stable and have been consistent and adherent to ARV medications for at least 2 years will be recruited as research assistants. Using standard training module developed and validated by a team of experts from Universiti Putra Malaysia and Hospital Sungai Buloh, a two-day onsite training of the research assistants on HIV prevention methods, care and treatment issues and how to respond to common questions related to medication adherence, including medication side effects, when asked by study participants, will be conducted. In addition to sending SMS and making telephone calls to patients, they will also be required to provide counseling support and provide guidance to patients (when required) in filling out medication adherence questionnaires during every clinic visits. Patients in the intervention group will be further divided into 2 sub-groups, each under the supervision of one research assistant, who will be responsible for providing them with counseling and psychosocial support, in addition to the care and management provided by the clinicians and nurses, throughout the duration of the study. Each patient in the intervention group would undergo a minimum of three (during clinic visits at month 1, month 3 and month 6) individual counselling sessions with the research assistants lasting an average of 15 minutes per encounter. An intervention manual containing the training modules and implementation guidelines will be provided to the research assistants as spiral-bound hard copy reference document, to guide their interactions with the patient and assure quality and uniformity in the implementation of the intervention.

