
**Data collection:** Research data will be collected using the below plan:

- **How:** 2 types (Primary and Secondary) of data will be collected from 3 main sources;

(a) Hospital medical records – Patients’ socio-demographic and clinic attendance data will be collected from hospital records; pharmacy records will be utilized for measuring adherence to drug refill appointments, while clinicians’ notes will be assessed for clinical information regarding weight, TB status, and OI index of clients (through standardized OI monitoring forms). Laboratory records will be accessed for baseline and follow-up CD4 count and viral load test results.

(b) Structured questionnaire and standardized medication adherence monitoring forms would be used to collect information from clients’ medication adherence self-reports during interaction with clinician/nurses/pharmacists at every scheduled clinic visit/appointment.

- **Who and When:** Socio-demographic (at enrolment) and clinic visit information (at every visit) will be collected by clinic medical record officers, laboratory information by laboratory scientists (at baseline, Months 3 and 6) and clinical and medication adherence information will be collected by clinicians/nurses/pharmacists at every client visit.

A log book on phone calls and text messages will also be recorded.

- **Duration:** Data will be collected over a 13 months period.
- **Questionnaire:** The Adult AIDS Clinical Trial Group (AACTG) adherence questionnaires (Chesney, M.A. et al, 2000) will be adapted with slight modifications, for the purpose of this study. Specialized questionnaires will be used at baseline and follow up. The questionnaire will be pre-tested on a population not included in the sample for validity and reliability.

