| Clinical (Wt, TB & OI status)                   | Clinician's notes       | Clinicians/nurses/adherence counsellors          | Every visit                                       |
| Immunological (CD4)
Virological (viral load) | Laboratory records      | Laboratory scientists                            | Baseline & 6mths                                  |
| Medication adherence                            | Adherence questionnaire | Research assistants/nurses/adherence counsellors | Baseline, then every visit (particularly 3&6mths) |

- **Data Storage:** All data generated from this study will be stored for a maximum of 3 years after the completion of the study, after which they will be destroyed. However, during this period they will remain joint intellectual property of Universiti Putra Malaysia and Hospital Sungai Buloh.

**Primary Outcomes:** The first primary outcome is (improved) patient adherence to ART at six months. This is assessed by self-report using a standardized questionnaire of the number of pills missed in the last 30 days and calculating percent adherence based on the expected number of doses taken and/or number of missed doses. Percent adherence will be analyzed as continuous variable and polytomous variable. Subjects will be considered as "Good adherence" when they achieve an optimal adherence cut of >95% of medications taken as directed with <3 missed doses in the last 30 days period. "Fair adherence" will be considered as 80-95% of medications taken as directed with 3-8 missed doses in the last 30 days period, while "Poor adherence" will be considered as <80% of medications taken as directed with >8 missed doses in the last 30 days period. Medication adherence will be assessed at each follow-up visit, particularly at months 3 and 6. The six month scheduled follow-up is the primary analysis but the three month assessment will allow for evaluating trends but is not the primary outcome.

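### The research assistants who deliver the intervention may also help collect the self-reported first primary outcome; the protocol contradicts itself on who collects it and leaves a route to over-reporting that differs by arm.

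*Protocol*

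**What the plan says.** All of this is in the protocol, section B (Research methodology).

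- **Delivery.** Under Intervention Protocol, the reminder module is "delivered via SMS and telephone calls by 2 PLHIV (research assistants"). The same text continues: "Patients in the intervention group will be further divided into 2 sub-groups, each under the supervision of one research assistant". That assistant gives counselling and psychosocial support for the whole study, with at least three sessions: "during clinic visits at month 1, month 3 and month 6) individual counselling sessions with the research assistants". Control patients get routine adherence counselling and no assigned assistant.
- **Help with the questionnaire.** The same paragraph asks the assistants to "provide guidance to patients (when required) in filling out medication adherence questionnaires during every clinic visits".
- **Who collects adherence data.** In the data collection table, the medication adherence row gives the responsible person as "Research assistants/nurses/adherence counsellors". The Who and When text says "clinical and medication adherence information will be collected by clinicians/nurses/pharmacists at every client visit", and item (b) of the same section places the self-report in the encounter with those staff. It does not mention research assistants.
- **What the questionnaire feeds.** Under Primary Outcomes: "The first primary outcome is (improved) patient adherence to ART at six months". It is measured by self-report of pills missed in the last 30 days. The second primary outcome, scheduled clinic attendance, comes from medical records supported by pharmacy pick-up records.
- **Blinding.** "Investigators will be blinded to intervention assignments". Nothing is said about whoever administers the questionnaire.
- **Limitations.** The protocol accepts that self-report exaggerates adherence and names refill records, CD4 count and viral load as ways to validate the answers. Pill count is not used.

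**The concern.** A self-report of missed pills is open to the wish to please. If patients in both arms overstate adherence to the same degree, the comparison is blurred but not tilted. If the overstatement is larger in one arm, it appears as a treatment effect. Randomisation gives no protection, because the difference arises after allocation.

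The protocol opens a route to such a difference. An assistant who has reminded, counselled and supported an intervention patient for months may also help that patient answer how many pills were missed, at the visit that supplies the primary time point. No control patient has that relationship with an assistant. What is at stake is the first primary outcome. No later analysis can separate a reporting difference from a real one using the self-report alone.

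**Working it through.** **Step 1. Set the passages side by side.**

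| Place in the protocol | Who handles adherence self-report |
|---|---|
| Intervention Protocol | Research assistants guide patients when required |
| Data collection, item (b) and Who and When | Clinicians, nurses, pharmacists |
| Data collection table, adherence row | Research assistants, nurses, adherence counsellors |

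These cannot all be the operating rule. Only nurses appear in both the text and the table. The sentence giving the assistants the questionnaire duty speaks of patients without naming an arm, and the table row is not split by arm, so the text does not settle whether assistants also help control patients.

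- If they help the intervention arm only, ascertainment differs by arm.
- If they help both arms, the helper still knows the allocation and has counselled one arm only. A difference can remain, though probably a smaller one.

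**Step 2. Timing.** The assistants' sessions are at months 1, 3 and 6. The primary analysis of adherence is at month 6. The protocol does not say whether the questionnaire comes before or after the session.

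**Step 3. The plan's own sample size.** From Sample size: SD 132, difference 50, two-sided alpha 0.05, power 80%.

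n = 2 × 132² × (1.96 + 0.842)² / 50² = 109.4, so 110 per group. 110 × 1.10 = 121. The stated figures reproduce with the difference squared in the denominator. The point here does not depend on this calculation; 121 and 110 are used only as arm sizes.

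**Step 4. What a reporting shift would do.** The documents give no size of reporting bias and no control rate of Good adherence. Both are assumptions.

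Suppose there is no true effect, the control rate is p, and reported Good adherence in the intervention arm is p + b. With n per arm:

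- pooled rate m = p + b/2
- SE₀ = √(2m(1 − m)/n)
- SE₁ = √([p(1 − p) + (p + b)(1 − p − b)]/n)
- chance of a significant result = Φ((b − 1.96·SE₀)/SE₁) + Φ((−b − 1.96·SE₀)/SE₁)

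Worked case p = 0.50, b = 0.10, n = 121: m = 0.55, SE₀ = 0.0640, SE₁ = 0.0636. First term: Φ((0.10 − 0.1254)/0.0636) = Φ(−0.40) = 0.345. The second term is negligible.

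| n per arm | p | b = 5 points | b = 10 points | b = 15 points |
|---|---|---|---|---|
| 121 | 0.50 | 12% | 35% | 66% |
| 121 | 0.60 | 13% | 37% | 70% |
| 121 | 0.70 | 14% | 43% | 80% |
| 110 | 0.50 | 11% | 32% | 62% |
| 110 | 0.70 | 13% | 40% | 76% |

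With b = 0 the rate is the nominal 5%. A shift of 15 points equals the effect that the Data analysis section says the trial is powered to detect, although that statement uses a 90% adherence cut-off.

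**Step 5. What would produce such a shift.** b = (1 − p) × share of non-adherent intervention patients helped × share of those helped who then report Good adherence. With p = 0.50, n = 121 and over-reporting shares of 10%, 20% and 30%:

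| Share helped | False shift (points) | Chance of a significant result |
|---|---|---|
| All | 5, 10, 15 | 12%, 35%, 66% |
| Half | 2.5, 5, 7.5 | 7%, 12%, 22% |
| A quarter | 1.25, 2.5, 3.75 | 5%, 7%, 9% |

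With p = 0.70 and all helped, the same shares give shifts of 3, 6 and 9 points and rates of about 8%, 18% and 36%.

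**The case against.** The best defence has four parts.

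- **Help is conditional.** Guidance is given only when required, item (b) puts the self-report in the encounter with clinic staff, and the table names assistants as one of three possible collectors. This stands. A reader might infer that an assistant sits beside every intervention patient as missed pills are reported, and does so only in that arm; the documents show neither. The lower rows of the last table reflect this.
- **No stated blinding is broken.** A reader might infer that unblinded collectors contradict the blinding statement. They do not: it covers investigators only, and people who send the reminders cannot be blind to them. The gap is that nothing protects the self-report when an assistant helps to collect it.
- **Exaggeration is acknowledged and there are checks.** This stands in part. Refill records, CD4 count and viral load are named as validation. But the caveat concerns exaggeration in general, not exaggeration that differs by arm, and the protocol gives no rule by which those sources correct or replace the self-report.
- **There is a second primary outcome.** Attendance comes from records and is untouched by this route. That protects the attendance result, not the adherence result.

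It could also be said that patients know their arm, so self-report may differ whoever hands over the form. This is true, and it limits what the fix can achieve. It is no reason to add a second, avoidable route.

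**Conclusion.** The point holds in this form. The protocol is inconsistent on who collects adherence data. On two of its three descriptions, unblinded staff who deliver the intervention may take part in ascertaining the first primary outcome, with a counselling session of theirs at the primary time point. This can make over-reporting differ by arm, whether or not they also help control patients.

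Upward bias in the intervention arm is the expected direction, but neither its presence nor its size can be read from the documents. A reader might conclude that the adherence result will be biased by a known amount; the documents do not support that. The figures are hypothetical and rest on an assumed control rate, assumed over-reporting shares and an assumed share of patients helped. Across the cases shown, the chance of a significant result with no true effect runs from barely above 5% to about 80%. Confidence is high on the dual role and the inconsistency, and low on size and on which arms are helped. It should be settled before data collection, because analysis cannot repair it afterwards.

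**What to change.** 1. Reconcile the Intervention Protocol, the Data collection text and the data collection table so that they name the same collectors. In both arms, only the clinic staff already named should administer the adherence questionnaire, with one script, before any contact with a research assistant at that visit.
2. Delete the assistants' questionnaire duty from the Intervention Protocol and remove research assistants from the adherence row of the table.
3. Report pharmacy-refill adherence, which is already collected, by arm as a supporting analysis of the first primary outcome.

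The cost is protocol wording, a fixed order of events at each visit and some extra clinic-staff time, which the documents do not let one quantify. The staff are already named, so the change adds no new role. The bias is reduced and not removed: patients still know their arm, and the clinic staff are not stated to be blinded.

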## RESEARCH APPROACH

### B. Research methodology

**Study Location:** The study will be conducted in Hospital Sungai Buloh, Selangor, Malaysia.

**Study Design:** It will be an experimental (randomized Controlled Trial) study design, single-blinded among newly diagnosed HIV positive patients who are eligible to commence ART from December 2013 to August 2014. Following enrollment and allocation to study arm, baseline adherence, clinical symptoms, CD4 count, viral load, Weight, TB status and Opportunistic infection index will be assessed and measured for the 2 groups, prior to the commencement of ART. The intervention group will receive appointment and medication reminders by text-messaging and telephone calls, in addition to standard care. Based on the Theory of Planned Behaviour Model (Ajzen, 1985), appointment reminders will be sent by Short Text Message (in Malay and English languages) three days prior to each individual client's scheduled appointment and telephone call reminders a day prior to the scheduled clinic appointment visits. Weekly short text messages will also be sent to clients to remind them of taking their medications. The control group will only receive standard care and paper-based appointment during clinic visits. Both groups of clients will be followed up for a period of 6 months on ART. Repeated CD4 count, viral load, Weight, TB status and OI index assessment and measurements will be conducted at 3 and 6 months, respectively to determine treatment outcome. Medication adherence will be measured using structured self-report questionnaires. Clinic visits will be measured through medical records of clinic attendance and clinicians' notes.

**Study Duration:** Recruitment and data collection will be from December 2013 to February 2015.

**Study population:** The study population is all HIV positive clients assessed and found to be eligible for ART commencement at Hospital Sungai Buloh, Selangor

**Inclusion criteria:** Age range of 15 to 65 years eligible to commence ART, able to read text messages and have a mobile phone access.

**Exclusion criteria:** Clients who are previously or currently on ART, foreigners & pregnant patients

**Sampling frame:** It is the list of all HIV positive clients assessed and found to be eligible for ART from December 2013 to August 2014 in Hospital Sungai Buloh, Selangor

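### The month-6 peer counselling session falls at the visit where the primary adherence self-report is taken, and the protocol neither puts the questionnaire first nor keeps the research assistants out of it

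*Protocol*

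**What the plan says.** Under Intervention Protocol, each intervention patient has at least three sessions of about 15 minutes: "during clinic visits at month 1, month 3 and month 6) individual counselling sessions with the research assistants". For the other arm, "The control group will receive standard care - routine adherence counseling only".

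Under Primary Outcomes, "The first primary outcome is (improved) patient adherence to ART at six months". It is measured by "self-report using a standardized questionnaire of the number of pills missed in the last 30 days", and "The six month scheduled follow-up is the primary analysis". Adherence is assessed at each follow-up visit, with months 3 and 6 singled out. Study Design adds that "Both groups of clients will be followed up for a period of 6 months on ART", so month 6 closes follow-up.

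The protocol describes who handles the adherence questionnaire in three places:

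- Intervention Protocol: the research assistants guide patients through it at clinic visits when help is needed.
- Data collection table, medication adherence row: research assistants, nurses and adherence counsellors are responsible.
- Data collection, Who and When: clinicians, nurses and pharmacists collect it. Research assistants are not named.

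The Blinding paragraph reads "Investigators will be blinded to intervention assignments" and names no other role.

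**The concern.** The first primary outcome depends on what a patient is willing to say about missed doses. At the visit where the answer counts, one arm has a scheduled one-to-one meeting with the peer who has been sending the reminders, and the other arm does not. The same peer may then help the patient fill in the form.

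If the meeting comes first, intervention patients may report fewer missed doses to please the counsellor, or because the talk has just reminded them of what is expected. Controls have no matching contact with a research assistant. An arm difference at month 6 could then reflect reporting as well as behaviour. The Limitations paragraph accepts that self-report exaggerates adherence. The issue here is that the exaggeration could differ between arms. An analysis plan cannot repair this once the data are collected.

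**Working it through.** **Timing**

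1. The recall window is the 30 days before the month-6 visit. Every dose in it has been taken or missed when the patient arrives.
2. The third session takes place at that visit. It therefore cannot alter the quantity being reported, and follow-up ends there, so no later assessment could show its effect.
3. It can affect the report only if it comes before the questionnaire. No section of the protocol says which comes first.
4. Month 3 has the same coincidence of session and questionnaire. That assessment serves for trend and is not the primary analysis.

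**Who handles the form**

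The three descriptions do not agree. Two let the research assistants help with or collect the questionnaire, and one leaves them out. Research assistants necessarily know the arm of their own intervention patients. If they help only those patients, the help itself differs by arm. If they help both arms, the helper is not blind to assignment.

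**Which outcomes are open to this**

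Self-reported adherence is. Clinic attendance comes from medical records, backed by pharmacy pick-up records, and CD4 count and viral load come from laboratory records. A conversation at the visit does not change those.

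**Possible size (illustration only)**

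The protocol has no figure to reproduce on this point. Assume no true effect, *n* = 121 per arm (from Sample size), a two-sided 0.05 test of good adherence, a true proportion *p* in both arms, and a share *s* of intervention patients without good adherence who nevertheless report it. The values of *p* and *s* are assumptions.

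- Reported proportion: *p* in control, *p*₂ = *p* + *s*(1 − *p*) in intervention.
- Spurious difference: *d* = *s*(1 − *p*).
- Rejection rate: 1 − Φ((1.96·se₀ − *d*)/se₁) + Φ((−1.96·se₀ − *d*)/se₁), where se₀ = √(2·p̄(1 − p̄)/*n*), p̄ is the mean of *p* and *p*₂, and se₁ = √((*p*(1 − *p*) + *p*₂(1 − *p*₂))/*n*).

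Worked case, *p* = 0.50 and *s* = 0.20: *p*₂ = 0.60, *d* = 0.10, se₀ = √(2 × 0.55 × 0.45/121) = 0.0640, se₁ = √((0.25 + 0.24)/121) = 0.0636. The upper term is 1 − Φ((0.1254 − 0.10)/0.0636) = 1 − Φ(0.40), about 0.345. The lower term is negligible.

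| True good adherence, both arms | *s* = 0 | *s* = 10% | *s* = 20% | *s* = 30% |
|---|---|---|---|---|
| 50% | 5% | 12% (*d* = 5 points) | 35% (10) | 66% (15) |
| 70% | 5% | 8% (3) | 18% (6) | 36% (9) |
| 80% | 5% | 7% (2) | 13% (4) | 24% (6) |

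With 110 per arm, the protocol's number before attrition is added, the rates are slightly lower: 12%, 32% and 62% in the first row. If the questionnaire is handed in first, this session contributes *s* = 0.

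**The case against.** A reader might infer that the month-6 session can only bias the answer. The documents do not support that. If clinic staff happen to take the questionnaire first, the session cannot touch it. The protocol also refers to an intervention manual with implementation guidelines, which is not shown and might set the order. The fault is that the protocol leaves the order open, and that stands.

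A reader might also infer that the session unmasks the trial. It adds little: patients and research assistants already know the arm from the messages, calls and earlier sessions, and no section claims that nurses or pharmacists are blinded. What remains is that clinic staff recording data may see who is counselled, and the Blinding paragraph does not say whether they count as investigators.

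The session content is not laid down as a talk on missed doses. It is described as counselling and psychosocial support. Controls have routine adherence counselling, so they are not shown to be free of adherence talk at the visit. The contrast that is established is the individual session with a research assistant.

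Finally, the Limitations paragraph plans to validate self-report against pharmacy refills, CD4 count and viral load. That helps interpretation, but it does not remove a one-sided bias from the primary outcome.

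**Conclusion.** The concern holds as a gap in the design of the primary measurement. The protocol schedules an intervention-only session at the visit of the primary self-report, does not put the questionnaire first, and contradicts itself on whether intervention staff handle the form. It therefore permits a reporting bias in one arm on self-reported adherence. It does not show that such a bias will occur, and the bias does not extend to recorded attendance, CD4 count or viral load.

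The size is unknown. The table depends wholly on assumed values of *p* and *s*. It shows only that modest differential misreporting would matter at this sample size. The spurious differences should not be read as fractions of the 15% impact under Data analysis, because that figure concerns adherence of at least 90% whereas good adherence is defined as above 95%.

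Fixing the order will not remove all self-report bias, since patients know whether they received reminders. It removes the part that arises from contact at the assessment visit. The change is worth making because it costs little.

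**What to change.** 1. In Intervention Protocol, state that at months 3 and 6 the adherence questionnaire is completed and handed in, in both arms, before any contact with a research assistant at that visit.
2. Reconcile Intervention Protocol, Data collection (Who and When) and the data collection table. The clinicians, nurses and pharmacists already named under Who and When should collect the questionnaire and give any help with it, in both arms, and the research assistants should not.
3. Under Blinding, list the roles that are blinded. Do not imply that patients, research assistants or clinic staff who can see the sessions are among them.

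Whether the month-6 session stays is for the sponsor to decide. The change needs no extra visits or procedures, and the staff are already named. The cost is some scheduling discipline in clinic and a less favourable blinding statement.
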